# A cluster randomised controlled trial of a ward-based intervention to improve access to psychologically-informed care and psychological therapy for mental health in-patients

**DOI:** 10.1186/s12888-022-03696-7

**Published:** 2022-02-03

**Keywords:** Cluster trial, Psychological therapy, Acute mental health, Inpatient, Process evaluation, Health economic analysis

## Abstract

**Background:**

There is good evidence that psychological interventions improve patient well-being and independent living, but patients on acute mental health wards often do not have access to evidence-based psychological therapies which are strongly advised by NICE guidance for severe mental health problems. The overall aim of this programme of work is to increase patient access to psychological therapies on acute mental health inpatient wards. Stage one of the programme (which is complete) aimed to identify barriers and facilitators to delivering therapy in these settings through a large qualitative study. The key output of stage one was an intervention protocol that is designed to be delivered on acute wards to increase patient access to psychologically-informed care and therapy. Stage two of the programme aims to test the effects of the intervention on patient wellbeing and serious incidents on the ward (primary outcomes), patient social functioning and symptoms, staff burnout, ward atmosphere from staff and patient perspectives and cost effectiveness of the intervention (secondary outcomes).

**Methods:**

The study is a single blind, pragmatic, cluster randomised controlled trial and will recruit thirty-four wards across England that will be randomised to receive the new intervention plus treatment as usual, or treatment as usual only. Primary and secondary outcomes will be assessed at baseline and 6-month and 9-month follow-ups, with serious incidents on the ward collected at an additional 3-month follow-up.

**Discussion:**

The key output will be a potentially effective and cost-effective ward-based psychological intervention that increases patient access to psychological therapy in inpatient settings, is feasible to deliver in inpatient settings and is acceptable to patients.

**Trial Registration number:**

ClinicalTrials.gov Identifier: NCT03950388. Registered 15^th^ May 2019. https://clinicaltrials.gov/ct2/show/NCT03950388

## Background

Severe mental health problems, such as schizophrenia and bipolar disorder, are characterised by profound disruptions in thinking, perception and everyday functioning [1]. More than 1.5 million people in England have a severe mental health problem. Symptoms and difficulties in functioning often start in young adulthood and can have a hugely distressing impact on the individual, family and friends. The care of people with severe mental health problems costs around £12 billion a year. This figure accounts for more than half of the mental health and social care budget and much of it is spent on acute inpatient admissions [2].

Between April 2017 and March 2018, 103,952 people who were in contact with mental health services spent time on mental health wards [3]. On average, it costs the NHS over £12,000 per acute inpatient admission [2]. Despite extremely high costs associated with inpatient care, inquiries and surveys of patient satisfaction highlight poor quality of care in these settings [1, 4, 5] and there are high levels of staff burn out and absenteeism [6].

Surprisingly, inpatients do not typically have access to evidenced-based psychological therapies, which are both wanted by patients and strongly advocated by NICE guidance for severe mental health problems, including Schizophrenia, Bipolar Disorder, Major Depression and Personality Disorder [7–10]. On the back of significant lobbying by patient and carer groups, the Mental Health Task Force [11] now advocates a ‘referral to treatment access’ standard for psychological therapy in acute inpatient care, meaning that NHS Mental Health Trusts will need to deliver timely, evidence-based psychological treatments in these settings.

Previous reviews demonstrate the benefits of psychological therapies for severe mental health problems, in terms of improvements in symptoms and reduced costs to the NHS [2, 12, 13]. However, recent systematic searches have found that very few trials of psychological therapies target inpatient wards [14]. Globally, at the time of writing a total of 68 studies have been carried out specifically in acute inpatient settings, but the majority of the studies are medium to low quality with low sample sizes, non-randomised designs, no blind assessment of outcomes, or not reporting -intention to treat analyses. Even when researchers use randomised designs, they often demonstrate poor randomisation methods and allocation concealment, with only two randomised control trials utilising an independent randomisation service and a large number not specifying the randomisation method at all. Furthermore, many studies target one particular type of problem only or specific diagnostic groups, such as early psychosis, depression or self-harm, thus excluding a significant proportion of patients on the ward. Although there is good evidence for psychological therapies from high quality trials with outpatients, we propose that existing evidenced-based psychological therapies need to be adapted for inpatient settings. The process of delivering therapy in inpatient settings is likely to present unique challenges which require empirical investigation. For example, patients are likely to be experiencing higher levels of distress and the relatively short length of patient stay may impact on the potential length of therapy. Additionally, there is an increased need to consider attitudes and relationships with other mental health workers. Relatedly, with the exception of our own study, which found a positive effect for Cognitive Behaviour Therapy compared to a control therapy on violence and risk management [15], most therapy trials have used patient symptoms as the primary outcome. We argue that serious incidents or so-called risky behaviours are more important outcomes to target and assess in inpatient settings because they: a) are more prevalent in inpatient settings; b) they prevent patients being discharged and therefore prolong length of stay; c) are highly distressing for all those involved, including patients themselves, carers, staff and other patients; and d) are extremely costly due to their impact on length of stay and the resource needed to manage them [16]. Despite the importance of serious incidents for inpatients, as research has focused on outpatient therapy, there is more limited evidence for the effects of psychological therapy on reducing serious incidents.

Given these gaps in knowledge, the first stage of this programme of research aimed to investigate barriers and facilitators to delivering therapy in inpatient settings with the end goal of developing an intervention protocol to maximise access to psychological therapy and psychologically-informed care on inpatient settings. This research took the form of: a) a review of 51 studies implementing psychosocial interventions on acute mental health wards [17]; b) a large qualitative study of 26 staff, 22 patient and 12 carer perspectives on inpatient therapy using semi-structured interviews; and c) two pilot studies where we implemented draft intervention protocols and used interviews to elicit stakeholder views on what aspects of the intervention and its delivery worked or did not work in practice [18]. The findings have resulted in the development of a model of how to deliver therapy on patient wards called TULIPS (Talk, Understand and Listen for In-Patient Settings). Key elements of the TULIPS model were agreed and prioritised during an expert consensus conference where nationally-drawn stakeholders, including national leaders in the development of psychological therapy for severe mental health problems, senior clinicians and managers working in inpatient setting and patient/carer representatives were asked to vote on questions posed by the research team [19]. Here we describe a protocol to evaluate the TULIPS intervention compared to treatment as usual, using a cluster randomised control trial. Anticipated benefits of the intervention are reductions in serious incidents on the ward, improved patient well-being and functioning and reduced staff burnout.

## Objectives

The primary objectives are: i) to assess the effectiveness of a psychological service model designed specifically for acute mental health wards; and ii) determine whether it reduces the occurrence of ward-level serious incidents and improves patient wellbeing. Secondary objectives are to: assess whether the intervention improves patient and staff perceptions of ward atmosphere, staff burnout, patient mental health symptoms and functioning; and to explore patient resource use to assess the cost-effectiveness of the psychological service model.

## Methods

### Trial design

The study is a single blind, pragmatic, cluster randomised controlled trial. The TULIPS model will be delivered at the ward level (cluster) and compared to treatment as usual within a superiority framework, using a one-to-one allocation ratio, with minimisation based on Trust and ward gender (male/female/mixed). The trial will include a 9-month internal pilot which will have clearly defined stop/go criteria. The comparator was selected on the basis of pragmatics and difficulty in identifying a suitable control comparator.

### Blinding and Randomisation

Once a site is recruited all eligible and consenting wards will be randomised. To maintain allocation concealment, the allocation will be conducted by an independent statistician at the King’s Clinical Trials Unit. Wards will be identified, and their Trust and ward gender (male/female/mixed gender) recorded. These will be entered into the minimisation program. If it does not make any difference to the balance on these variables which group is chosen, the ward will be allocated randomly. Otherwise, it will be allocated to the group which would make the two groups better balanced on these variables.

Members of the Trial Steering Committee (TSC), study statisticians, health economists and outcome assessors will be blinded to treatment allocation while the trial is ongoing. If the outcome assessors know (or suspect) they have been unblinded, this will be recorded on an unblinding form. For practical reasons linked to the setup and delivery of the intervention, some members of the research team and will not be blinded, including the Project Manager and Chief Investigator. Due to the nature of the intervention, participants and intervention delivers will not be blinded following the commencement of the intervention. Ward allocation will however, be concealed from potential participants until the completion of baseline measures to reduce the risk of selection bias.

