### Recruitment

The baseline data will be gathered after the ward has been randomised. This is not the optimal design as it runs the risk of selection bias and in particular the control wards not being motivated to engage in the intervention. However, it was deemed to be the most practical solution due to difficulties in organising training for all ward staff at the start of the intervention (at least 4 weeks are needed to schedule rosters, backfill ward staff and book suitable rooms) and the importance of recruiting patients just prior to the start of the intervention (so they are exposed to at least some elements of it before being discharged from the ward). In order to circumvent the risks associated with early randomisation, the outcome of the randomisation will only be disclosed to a few key people (see below).

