### Sample size

The recruitment target is thirty-four wards. Based on a recent survey of acute inpatient wards across the NHS, it is estimated that there will be an average of 24 beds per ward (range 18-30) giving a pool of 816 patients at baseline across 34 wards. Based on the same survey, it is estimated that there will be an average of 25 staff per ward giving a potential pool of 850 staff across 34 wards. Based on trials of psychological therapy in inpatient settings [27, 30] it has been conservatively estimated that recruitment rates for the completion of individual level outcome measures at baseline will be 80% of eligible staff and 50% of eligible patients giving a pool of 680 staff and 408 patients.

For the primary outcome of number of serious incidents on the ward, assuming 5.22 mean number of events in the control arm [31], 16 wards per arm has more than 80% power to detect a reduction in mean number of events to 3.13 (40% relative reduction), assuming a poisson distribution for the outcome. To allow for possible dropout of a ward, we will recruit 34 wards in total.

For the individual level health related primary outcome (WEBWBS) and other individual level secondary outcomes, we used the –clustersampsi- command in Stata. We assume a between group effect size of 0.4 and an intra-cluster correlation coefficient of 0.05. We allow for a baseline-endpoint correlation of 0.3, which we suggest is conservatively low given the short time span between baseline and endpoint. We specified 85% power, 5% significance level, and calculated the average cluster size (i.e. how many participants were required to be recruited in each cluster). The optimal design for these parameters requires 9 participants per cluster. This leads to a total sample size per arm of 153, and 306 for the analysis set. Accounting for attrition of 20%, by making an adjustment to this value, 383 participants are required at baseline. This assumes that attrition is consistent across treatment arms and clusters. Therefore the aim is to recruit 34 clusters with 11 participants in each cluster, giving a total sample size at baseline of 384. Adjustments will be made for additional covariates in order to preserve 85% power against a larger observed ICC value or a weaker observed baseline-endpoint correlation.

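### Minimisation is random only at ties, so a ward's arm can be partly inferred from sister wards in the same Trust, while participants are recruited after randomisation

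*Protocol article*

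**What the plan says.** Under Trial design, the protocol article sets out allocation "using a one-to-one allocation ratio, with minimisation based on Trust and ward gender (male/female/mixed"). Blinding and Randomisation then gives the algorithm in two sentences. At a tie: "If it does not make any difference to the balance on these variables which group is chosen, the ward will be allocated randomly". In every other case: "Otherwise, it will be allocated to the group which would make the two groups better balanced on these variables". No probability below 1 is mentioned for the non-tied case.

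The same section says "Once a site is recruited all eligible and consenting wards will be randomised" and that "the allocation will be conducted by an independent statistician" at an external unit. Outcome assessors and study statisticians are to be blind, suspected unblinding of assessors is to be recorded, and "some members of the research team and will not be blinded, including the Project Manager and Chief Investigator". Participants and those delivering the intervention stop being blind once it starts on their ward. Potential participants are not told the arm until baseline measures are complete.

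Under Recruitment: "The baseline data will be gathered after the ward has been randomised". The authors acknowledge that this carries a risk of selection bias, explain why they accept it, and offer restricted disclosure of the allocation as the mitigation.

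**The concern.** Restricted disclosure protects a ward only if its arm cannot be worked out by other means. Here the two balancing factors are visible to anyone on site, and a Trust's wards are pushed towards an even split. The arm of a ward whose intervention has started is evident there. Someone recruiting or assessing on a sister ward may then have better than even odds of knowing its arm.

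This matters more than usual because consent and baseline assessment come after randomisation. There is room for selection. Under Participant eligibility, the researcher, with the clinical team, judges whether a patient can concentrate well enough to take part. Under Sample size, only half of eligible patients are expected to enrol. WEMWBS is collected by assessors whose blinding could be eroded in the same way.

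**Working it through.** The protocol gives no predictability figure, so there is none to reproduce. The check simulates the stated rule.

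**Inputs from the protocol.** 34 wards (Sample size: "The recruitment target is thirty-four wards"); 1:1 allocation; two factors, Trust and ward gender with three levels; probability 1 to the balance-improving arm; 50:50 at ties.

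**Inputs assumed and varied, because the protocol does not give them.** 4 to 14 Trusts of near-equal size; gender mix of equal thirds or 25/25/50; wards entered Trust by Trust or in mixed order; imbalance measured as the sum of absolute or of squared marginal differences.

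**What the rule does.** Let d be the current difference in ward counts between arms within one margin (this Trust, or this gender). With the absolute measure, adding the ward to one arm rather than the other changes that margin's contribution by |d+1| − |d−1|. This is 0 if d = 0, and +2 or −2 otherwise. Each margin therefore casts one vote for its lagging arm or abstains. A ward is random only if both margins abstain or the votes cancel; otherwise it is forced.

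**Rule as written.**
- Share of allocations forced by earlier ones: about 61-69%.
- Correct guess with the full ledger = forced share + 0.5 × (1 − forced share). At 0.61 this is 0.61 + 0.195 = 0.805; at 0.69 it is 0.69 + 0.155 = 0.845. The simulations give the same 80-85%.
- Correct guess knowing only earlier wards in the same Trust (name the lagging arm, toss a coin if level): about 65-72%.
- All wards of a Trust entered in one batch, with only earlier Trusts known: 55-63% before allocation.
- After the batch, knowing every other ward in that Trust: 78-88% for 4, 6, 8, 10 or 14 Trusts, and about 70% for 12, where most Trusts have three wards and knowing two of them often leaves a level count.
- Mean absolute difference in arm totals: about 0.5-0.9 wards (0.4-1.0 at the extremes).

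**With probability 0.8 for the balance-improving arm.**
- No allocation is certain.
- Full-ledger guess = 0.8 × n + 0.5 × (1 − n), where n is the non-tied share, now about 0.64 to 0.756. At 0.64 this is 0.512 + 0.18 = 0.692; at 0.756 it is 0.605 + 0.122 = 0.727. The simulations give about 69-73%.
- Own-Trust guess: about 59-64%.
- After a batch, knowing every other ward in the Trust: about 68-73% for 4, 6, 8, 10 or 14 Trusts.
- Mean absolute difference in arm totals: about 1.4-1.8 wards (1.3 at the lowest).

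**The case against.** **The high figure belongs to people it does not affect.** Guessing at 80-85% needs the ledger across all Trusts. The people the protocol names as unblinded already know the current ward's arm, so prediction adds nothing for them. Nothing says that recruiters, assessors or ward staff hold such a ledger. This stands. The figure to use is the own-Trust one.

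**Selection of wards is protected.** Wards are eligible and consenting before randomisation, all are randomised, and an independent statistician allocates. The text can also be read as entering a site's wards together, which brings prediction before allocation down to 55-63%. This stands too. It does not cover inference after allocation, which is when participants are recruited.

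**The participant-level risk is disclosed and mitigated.** Disclosure is restricted, suspected unblinding is logged, and all eligible staff and patients are to be approached. These measures limit the harm, but none makes the arm harder to infer from sister wards. Randomising before recruitment remains the main weakness, and the authors admit it; the allocation rule adds to it.

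**Stronger readings the documents do not support.** A reader might infer that concealment is defeated or that bias has occurred; the documents show neither. A reader might also infer that one intervention ward settles the arm of a same-gender ward in that Trust. It does not, because gender totals across all Trusts also count: in Trust-by-Trust runs the second such ward falls in the opposite arm about 84-90% of the time, and less often when entry is mixed. Nor do the documents show that sites knew the algorithm before allocation, although the own-Trust guess requires only an expectation that a Trust's wards will be split.

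**The fix is partial.** Balancing within Trust is itself informative, so with 0.8 the same-gender figure is still about 68-72%.

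**Conclusion.** The concern holds as an avoidable weakness that is cheap to reduce. The rule as written is deterministic except at ties. About 61-69% of allocations are forced, and someone who knows only earlier wards in their own Trust is right about 65-72% of the time. The figures rest on assumed numbers of Trusts, gender mixes and entry orders, but the conclusion held across the range tried. They also suppose that the observer has learned the arms of sister wards, which blinded staff are not meant to know.

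The exposure lies with local staff, recruiters and assessors during recruitment and follow-up of the baseline cohort. It therefore bears mainly on WEMWBS and the other individual-level outcomes. Serious incidents are ward counts from routine reporting, so selective enrolment cannot change them; only the assessors' collation and 25% check could be touched. Patients recruited at 6 months for VOICE are, by the protocol's own account, not blind to their ward's condition, so predictability adds little to their own knowledge of the arm.

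**What to change.** For wards still to be randomised:

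1. Allocate to the balance-improving arm with a probability below 1, for example 0.8, and keep simple randomisation at ties.
2. State that all wards of a site are entered together, in random order.
3. Keep the probability out of site-facing documents.
4. Adjust for Trust as well as ward gender in the analysis models, unless the statistical analysis plan already does so. Data analysis names a ward-gender effect for ward-level outcomes and no Trust term, although Trust is a minimisation factor.

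If the program already contains a random element, correct the description. If allocation is complete, report the rule actually used and whether assessors' unblinding records cluster in Trusts with several wards.

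**Cost.** One program parameter and a few sentences. Mean arm imbalance rises from about 0.5-0.9 to 1.4-1.8 wards of 34, roughly one extra ward. As a fixed effect, Trust uses one fewer degree of freedom than the number of Trusts, so 3 to 13 over the assumed range of 4 to 14; with 34 wards a random Trust effect may be preferable at the upper end. Inference within a Trust is reduced, not removed.

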### Participants

Participants will include patients and staff who are based on an acute mental health ward recruited to the study. See Fig. 1 for participant flow through the study. See Fig. 2 for consort.

**Fig. 1 Fig1:**
[figure not shown]
Participant flow through study

**Fig. 2 Fig2:**
[figure not shown]
Consort diagram

## Eligibility criteria

### Ward eligibility

Inclusion criteria for wards will be acute mental health wards. Exclusion criteria will be: wards that have a specialist function, such as organic impairment, intensive care or rehabilitation; and wards that already have more than two sessions of dedicated psychological therapy input per week. This latter criterion is to ensure treatment as usual does not include significant elements of the intervention we are aiming to test.

